**9.2** **Anticipated Adverse Events**

　　The anticipated adverse events (including surgical complications) in this study are as follows.

1) Intraoperative Complications

• Dural injury

• Massive bleeding (2000 ml or more)

• Nerve injury (spinal cord)/Nerve injury (nerve root)

• Major vessel injury/Vertebral artery injury/Other arterial injury

• Vertebral body injury/Transverse process fracture

• Misidentification of level

• Conversion to conventional method

2) Early postoperative complications (surgery-related)

• Vascular injury (major vessel injury/Vertebral artery injury/Other vascular injury)

• Epidural hematoma

• Neurological/muscle strength related (Postoperative upper limb paralysis/Postoperative lower limb paralysis/Postoperative sensory nerve paralysis/Bladder/rectal dysfunction/Other complications)

• Spinal support tissue injury (Vertebral body injury/Ligamentum flavum fracture)

• Dural injury (Cerebrospinal fluid leak/Meningitis/Intracranial lesion [Subdural hematoma, etc.])

• Implant-related (Implant fracture, Implant dislocation, Screw malposition)

• Surgical Site Infection (Superficial/Deep)

• Misidentification of level

• Other (Postoperative complications due to positioning), Eye complications [Corneal injury, etc.], Blindness, Dysphagia

Early postoperative complications (Systemic complications)

• Acute heart failure

• Myocardial infarction

• Pulmonary infarction

• Pulmonary embolism

• Peripheral venous thrombosis (symptomatic)

• Respiratory failure

• Aspiration pneumonia

• Pneumonia

• Atelectasis

• Pulmonary edema

• Cerebral infarction

• Postoperative delirium

• Dementia

• Intestinal Obstruction

• Pseudomembranous Colitis

• Gastrointestinal Perforation/Gastric Perforation

• Pancreatitis

• Hepatitis

• Cholangitis

• Acute Renal Failure

• Urinary Tract Infection

• DIC

• Sepsis

• Fractures Due to Falls During Hospitalization

• Other

3) Late Postoperative Complications

• Neurological symptoms

• Worsening of local kyphosis

• Worsening of slippage

• Systemic complications/comorbidities

• Instrument-related (loosening/dislocation)

• Infection (superficial/deep)

• Other

**9.3　Response to Adverse Events, Surgical Complications, and Malfunctions**

**9.3.1　Response to Adverse Events, Surgical Complications, and Malfunctions**

When the attending surgeon identifies an adverse event (including surgical complications; the same applies hereafter) or malfunction, they shall immediately take appropriate measures and record the details accurately in the original source documents (e.g., medical history records) and the case report form without discrepancy. Furthermore, if protocol treatment is discontinued or treatment for the adverse event becomes necessary, the subject must be informed accordingly (refer to “15. Matters Concerning Monetary Payments and Compensation” regarding compensation for adverse events).

**9.3.2　Response to Serious Adverse Events, Surgical Complications, and Malfunctions**

For all serious adverse events (including surgical complications; the same applies hereafter) and any serious adverse events suspected to be related to the study occurring after study completion (termination), appropriate treatment must be promptly administered to the research subject, and the principal investigator must be notified. The principal investigator must promptly report to the head of the research institution (hospital director) using the designated form ([Safety Report Form 2], etc.) (in principle, the initial report within two weeks) and report to the Ethics Review Committee or Clinical Research Oversight Committee*. Notify all heads of research institutions (hospital directors) promptly as well.

*: Report via Tokyo University of Science's “Ethics Review Application System”.

**9.3.3　Response to Unforeseen Serious Adverse Events, Surgical Complications, or Malfunctions**

When unforeseen serious adverse events (including surgical complications; the same applies below) occurs, promptly administer appropriate treatment to the research subject and report to the Principal Investigator. The Principal Investigator shall promptly (principally within two weeks for the initial report) report to the head of the research institution (hospital director) using the prescribed form ([Form An1], etc.), and report to the Ethics Review Committee or Clinical Research Monitoring Committee. Notify the head of all research institutions (hospital director).

*: Report via Tokyo University of Science's “Ethics Review Application System”.

※ Events described in “9.2 Anticipated Adverse Events” are considered known/predictable events.

## **9.4　Observation of Research Subjects Following Adverse Events, Surgical Complications, or Malfunctions**

Research subjects shall be observed following the occurrence of an adverse event (including surgical complications; the same applies hereafter) until the adverse event resolves or recovers, or until the attending surgeon determines that follow-up is unnecessary.

**10．Matters Concerning Statistical Analysis**

An overview of the statistical analysis plan for this study is provided below. Details of the statistical analysis plan are specified separately in the Statistical Analysis Plan. While the Statistical Analysis Plan may alter analysis methods, etc., from the overview in this Study Protocol, if changes significantly impact the interpretation of this clinical study's results—such as alterations to the definition of primary endpoints or analysis methods—this Study Protocol shall be revised.

**10.1　Analysis Population**

**10.1.1　Full Analysis Set (FAS)**

This population is defined as the group of cases enrolled and randomized in this study who received the protocol treatment (cervical laminoplasty). However, cases with no data whatsoever after randomization will be excluded.

**10.1.2　Safety Analysis Set (SAS)**

This is defined as the population of all cases enrolled and randomized in this study who underwent the protocol treatment (cervical laminoplasty).

**10.2　Target Enrollment Numbers and Rationale**

Target enrollment: 216 cases

(Control group [mini-plate]: 108 cases, Test treatment group [suture-anchor]: 108 cases)

[Rationale]

Regarding the primary endpoint, the recovery rate in cervical JOA scores before and after surgery, a retrospective pilot study at Saiseikai Kawaguchi General Hospital, which used a patient population similar to this study, reported rates of 49.9±22.8% (21 cases) for the plate method and 52.6±32.9% (20 cases) for the suture anchor method (unpublished data).

Furthermore, a previous report^3)^ indicated that the MCID for compressive myelopathy is 52.8%. Based on the pilot study and past MCID findings, the recovery rate in cervical JOA scores for the control group (plate method) in this study was set at 50% (standard deviation 40%), with a non-inferiority margin of 20%. With a significance level (one-sided) of 0.025 and

and a power of 0.9, the required sample size for both groups combined is 172 cases. Anticipating approximately 20% dropout, the target sample size for both groups combined was set at 216 patients.

This target enrollment number is treated as an anticipated enrollment number, and exceeding this anticipated number is permitted. However, the Principal Investigator (PI) shall manage the cumulative actual enrollment numbers across all participating institutions to ensure the total number of cases does not exceed the study's target enrollment. If additional enrollment is required to meet the overall study target, prior approval must be obtained from the Ethics Review Committee or equivalent body.

**10.3　Case Handling**

In principle, decisions regarding the handling of enrolled cases shall be made by the Principal Investigator and the Statistician, after consultation. Decisions on case handling arising from new issues shall also be made by the Principal Investigator and the Statistician, after consultation. In all cases, the details of the case handling decisions shall be documented.

**10.4　Data Handling**

Data handling during data collection and analysis shall generally follow the principles outlined below. In case of doubt, the principal investigator and the person responsible for statistical analysis shall consult and decide. Missing values shall not be imputed. Details shall be specified separately in the statistical analysis plan.

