**7.6　 Individual Research Discontinuation Criteria**

The study will be discontinued if any of the following criteria are met.

1) If the protocol treatment (laminoplasty) cannot be performed within 90 days of registration.

2) If the research subject voluntarily requests to withdraw consent.

3) If, after registration, imaging or clinical diagnosis determines that laminoplasty is not indicated.

4) If intraoperative findings indicate laminoplasty is impossible or if cervical fusion is performed instead of laminoplasty.

5) If intraoperative complications (lamina fracture, vertebral body fracture) necessitate fixation during or after surgery

6) If a major deviation from the protocol is identified, such as violation of the Clinical Research Act and its enforcement regulations, selection criteria, or exclusion criteria

7) If compliance with the protocol becomes impossible

8) If the subject becomes pregnant

9) If the entire study is discontinued

10) If the research subject dies

11) Other cases where the principal investigator or attending surgeon determines continuation of the study is difficult

*The protocol treatment discontinuation date is defined as: the date of determination for cases 1-3), 5)-9), and 11); the surgery date for case 4); and the date of death for case 10).

[Rationale]

These criteria were established to ensure ethical research conduct and to safeguard the safety of research subjects.

[Procedure upon Discontinuation]

When discontinuing the study due to meeting discontinuation criteria, the principal investigator and co-investigators shall take appropriate measures for the subject and clearly document the date/timing of discontinuation, reason, and course of events in the medical records.

Furthermore, if consent is withdrawn after the start of the study treatment, efforts shall be made to clarify whether the cause is due to lack of efficacy of the drug, adverse events (or disease, etc.), or incidental events

(such as relocation). If clinically significant abnormalities (including laboratory values) are identified, appropriate tests shall be performed, and follow-up shall continue until values return to medically acceptable ranges or until the attending surgeon determines follow-up is unnecessary. For adverse events (or diseases, etc.) persisting after study discontinuation, follow-up shall continue until the event resolves or the attending surgeon determines follow-up is unnecessary.

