**10.5.2　Analysis of Primary Endpoints**

・Recovery Rate in Cervical JOA Score Before and After Surgery

For FAS participants, calculate the least squares mean and its 95% confidence interval for the cervical JOA score recovery rate at 1 year post-surgery using analysis of covariance. Also calculate the between-group difference in least squares means (suture anchor method vs. plate method), its 95% confidence interval, and the p-value. The analysis model included the following covariates: group, preoperative JOA score, age (≤64 years, 65–74 years, ≥75 years), sex, and preoperative diagnosis (cervical spondylotic myelopathy (CSM), ossification of the posterior longitudinal ligament (OPLL)).

The suture-anchor method will be considered non-inferior to the mini-plate method if the lower limit of the 95% confidence interval for the least squares mean difference between groups at 1 year postoperatively exceeds –20%. Additionally, as a secondary analysis, a Mixed-effects Model for Repeated Measures (MMRM) analysis will be performed using the first available subject (FAS) population, with the recovery rate in cervical JOA scores at 1 year and 2 years postoperatively relative to preoperatively as the response variable. The analysis model will include the following as fixed effects: group, time point, group-time interaction, preoperative JOA score, age (≤64 years, 65–74 years, ≥75 years), sex, and preoperative diagnosis (CSM, OPLL). Using this model, the least squares mean and 95% confidence interval for the recovery rate in cervical JOA scores before and after surgery at 1 year and 2 years postoperatively will be calculated. Additionally, the between-group differences in the recovery rate of cervical JOA scores before and after surgery at 1 year and 2 years postoperatively, along with their 95% confidence intervals and p-values, were calculated.

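### The no-imputation rule in 10.4 leaves the non-inferiority verdict without a stated test against outcome-related loss inside the FAS, because the MMRM is only a partial, missing-at-random check

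*Protocol*

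**What the plan says.** - **Missing data.** Protocol 10.4: "Missing values shall not be imputed". The same paragraph says data handling will generally follow its principles and leaves details to a separate SAP.
- **Expected loss.** Protocol 10.2: "Anticipating approximately 20% dropout, the target sample size for both groups combined was set at 216 patients". The split is "Control group [mini-plate]: 108 cases, Test treatment group [suture-anchor]: 108 cases".
- **Primary analysis.** Protocol 10.5.2 analyses "the cervical JOA score recovery rate at 1 year post-surgery using analysis of covariance" in the FAS. Non-inferiority is declared if the lower 95% limit for suture-anchor minus mini-plate is above -20.
- **Secondary analysis.** The same section plans an MMRM in the FAS on the 1-year and 2-year recovery rates. It attaches no decision rule to it.
- **When JOA is scored.** Sections 7.2.1 and 8.2 give three occasions: before surgery, 1 year and 2 years.
- **Who is in the FAS.** Section 10.1.1 takes randomized patients who received laminoplasty, less those with no data at all after randomization.
- **Who stops.** Section 7.6 lists, among other criteria, "If intraoperative complications (lamina fracture, vertebral body fracture) necessitate fixation during or after surgery", and death. After discontinuation it asks for follow-up of clinically significant abnormalities and adverse events. It does not mention the 1-year JOA.

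**The concern.** With imputation barred, only patients who have a 1-year score enter the deciding model. In a superiority trial a modest loss of poor outcomes is often tolerable. In a non-inferiority trial, losing poor outcomes from the test arm moves the estimate towards the conclusion that the sponsor hopes to reach.

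Some loss inside the FAS can follow from the surgical course. A patient whose laminoplasty is completed and who then needs fixation for a fracture meets the FAS definition, yet is discontinued under 7.6 with no stated duty to score JOA at 1 year. Fracture may plausibly depend on the fixation method, which is what the trial compares.

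The no-imputation sentence makes this more than a detail left for the SAP. As worded, it rules out the usual not-at-random check, in which missing values are imputed and then shifted.

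**Working it through.** **1. Reproduce the plan's sample size.** Inputs from 10.2: the control recovery rate "was set at 50% (standard deviation 40%), with a non-inferiority margin of 20" percentage points; one-sided alpha 0.025; "and a power of 0.9, the required sample size for both groups combined is 172 cases". The true difference is not stated and is taken as 0.
- Normal approximation: 2 × (1.960 + 1.282)² × 40² / 20² = 84.1, so 85 per arm.
- With the t distribution, power is 0.8999 at 85 and 0.9032 at 86 per arm. So 86 per arm, or 172.
- 86 / 0.8 = 107.5, so 108 per arm, or 216.

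The plan's figures reproduce. If 172 patients have a 1-year score, power is 90.3%, so the exposure is bias rather than power.

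**2. Formula for the bias.** Let f be the fraction of an arm's FAS patients without a 1-year score, and d the number of points by which their recovery falls short of the observed patients in that arm.

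Bias in (anchor - plate) = f_anchor × d_anchor - f_plate × d_plate

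The documents give no value for d. The range of 10 to 30 is an assumption.

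**3. Error at the margin.** SE = 40 × √(2/86) = 6.10. The critical t on 170 df is 1.974, so the half-width is 12.04. With a true difference of -20, the chance of declaring non-inferiority is P(T > 1.974), where T is noncentral t with 170 df and noncentrality bias/SE. For simplicity, 86 per arm are analysed throughout and covariate adjustment is ignored.

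Only missing suture-anchor patients worse (d_plate = 0):

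| d_anchor | f = 0.20: bias, error | f = 0.113: bias, error |
|---|---|---|
| 0 | 0, 2.5% | 0, 2.5% |
| 10 | 2.0, 5.1% | 1.13, 3.8% |
| 20 | 4.0, 9.5% | 2.27, 5.6% |
| 30 | 6.0, 16.3% | 3.40, 8.0% |

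The second column assumes that half of the 216 - 172 = 44 losses never enter the FAS. The FAS is then 216 - 22 = 194, and the missing fraction is 22/194 = 11.3%.

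The pooled pilot SD is √[(20 × 22.8² + 19 × 32.9²)/39] = 28.2. With it and f = 0.20, the errors are 6.7%, 15.0% and 28.3%. The last needs a deficit larger than one SD.

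**4. Other patterns.**
- Equal f and equal d in both arms: bias 0, error 2.5%.
- Only missing plate patients worse (f = 0.20): bias -2, -4 or -6. Error falls to 1.1%, 0.5% or 0.2%. Power at a true difference of 0, with noncentrality (20 + bias)/6.10, falls from 90.3% to 83.5%, 74.2% or 62.6%.

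**5. How large a deficit would overturn a positive result.** With 22 of 108 missing (f = 0.204), only missing anchor patients worse, and the complete-case SE, the tipping value is (observed difference - 12.04 + 20) / 0.204.

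| Observed difference | Tipping deficit (points) |
|---|---|
| +2.7 (the pilot difference) | 52 |
| 0 | 39 |
| -2.5 | 27 |
| -5 | 15 |
| -7.5 | 2 |

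**6. What the MMRM adds.** It brings in a patient who misses year 1 but is scored at year 2. A patient with neither score contributes no outcome to either model. It assumes missing at random, with no postoperative JOA before year 1 to inform that assumption. Under 10.7 the primary analysis follows the last patient's 1-year visit, when some 2-year scores will not yet exist.

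**The case against.** A reader might infer that nothing planned checks for missing data at all. The documents do not support that: the MMRM in 10.5.2 uses every available 1-year and 2-year score without imputation and is a real, if weak, check under missing at random. The SAP is not at hand, 10.4 leaves details to it, and section 10 allows it to alter methods. A sensitivity analysis may therefore be planned there. What stands is that an imputation-based one would contradict the flat sentence in 10.4, and section 10 itself asks for a protocol revision where a change affects interpretation significantly.

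A reader might also count conversion to fusion in place of laminoplasty as missing data here. Those patients did not receive laminoplasty and are outside the FAS under 10.1.1. The same holds for patients never operated on. Their exclusion is a question about the FAS definition, and it means that loss within the FAS may be below 20%.

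The direction is open too. Section 3.2 reports reclosure of 1.8-5.5% for suture anchors and 3.4-13.3% (screw dislodgement) for mini-plates. Plate screws are placed in the lamina itself, so fracture-related loss could as plausibly fall on the plate arm. This objection stands in full: the error rates illustrate one pattern and do not predict it.

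Finally, the verdict is not fragile everywhere. At an observed difference of 0 it takes a one-arm deficit of about 39 points to overturn it.

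**Conclusion.** The point holds as a gap in robustness. It does not show that the trial's error rate is inflated. The protocol fixes a no-imputation rule, expects about 20% dropout, and rests non-inferiority on observed 1-year scores, with only a missing-at-random secondary model beside it. Outcome-related loss inside the FAS, for example after fixation for a fracture, would go untested on the stated plan.

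The size depends on three assumptions that the documents do not supply: the share of FAS patients without a 1-year score, their deficit, and whether the deficit is confined to one arm. Under the adverse one-arm pattern at SD 40, error at the margin is about 5% to 16% with 20% missing and about 4% to 8% with 11% missing. It is unchanged if both arms are affected alike, and lower than nominal if the plate arm is the one affected. The gap matters most if the observed difference is clearly negative: at -5, a deficit of about 15 points is enough to reverse the conclusion.

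Multiple imputation alone would not close the gap. From baseline covariates and any 2-year score it makes the MMRM's assumption with nearly the same information.

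**What to change.** 1. **Protocol 10.4:** limit the sentence to the primary model. For example: missing 1-year recovery rates are not imputed in the primary ANCOVA; sensitivity analyses may use imputation as set out in 10.5.2 and the SAP.
2. **Protocol 10.5.2 and SAP:** add a delta-adjusted tipping-point analysis of the 1-year difference. Vary delta separately in each arm, report the combinations at which the lower 95% limit reaches -20, and state how patients who die before 1 year are handled, since a recovery rate cannot be observed for them.
3. **Protocol 7.6:** state that the 1-year JOA is still collected after discontinuation of protocol treatment unless the patient withdraws consent. This concerns data collection only and leaves clinical management as it is.

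The cost is some wording, one extra analysis whose result may be less favourable, and continued collection of a score at a visit already in the schedule. The third change is the most urgent, because scores not taken after discontinuation cannot be recovered later.

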**10.5　Statistical Analysis Items and Analysis Plan**

All efficacy evaluations will be conducted using the FAS population.

Safety analyses will be conducted using the SAS population.

Details of the statistical analysis will be specified in a separate statistical analysis plan created before data locking.

**10.5.1　Summary of Subject Background**

The distribution and summary statistics of subject background data will be calculated for each analysis population, by allocation group. For nominal and ordinal variables, the frequency and proportion of categories will be shown by allocation group. For continuous variables, summary statistics (number, mean, standard deviation, minimum, median, maximum) will be calculated by allocation group.

**10.5.2　Analysis of Primary Endpoints**

・Recovery Rate in Cervical JOA Score Before and After Surgery

For FAS participants, calculate the least squares mean and its 95% confidence interval for the cervical JOA score recovery rate at 1 year post-surgery using analysis of covariance. Also calculate the between-group difference in least squares means (suture anchor method vs. plate method), its 95% confidence interval, and the p-value. The analysis model included the following covariates: group, preoperative JOA score, age (≤64 years, 65–74 years, ≥75 years), sex, and preoperative diagnosis (cervical spondylotic myelopathy (CSM), ossification of the posterior longitudinal ligament (OPLL)).

The suture-anchor method will be considered non-inferior to the mini-plate method if the lower limit of the 95% confidence interval for the least squares mean difference between groups at 1 year postoperatively exceeds –20%. Additionally, as a secondary analysis, a Mixed-effects Model for Repeated Measures (MMRM) analysis will be performed using the first available subject (FAS) population, with the recovery rate in cervical JOA scores at 1 year and 2 years postoperatively relative to preoperatively as the response variable. The analysis model will include the following as fixed effects: group, time point, group-time interaction, preoperative JOA score, age (≤64 years, 65–74 years, ≥75 years), sex, and preoperative diagnosis (CSM, OPLL). Using this model, the least squares mean and 95% confidence interval for the recovery rate in cervical JOA scores before and after surgery at 1 year and 2 years postoperatively will be calculated. Additionally, the between-group differences in the recovery rate of cervical JOA scores before and after surgery at 1 year and 2 years postoperatively, along with their 95% confidence intervals and p-values, were calculated.

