**5.3　 Case Registration and Allocation Method**

1) Case Registration Method

The principal (or co-principal) investigator confirms that patients who have provided written informed consent meet all inclusion criteria and do not meet any exclusion criteria. Subsequently, personnel involved in this clinical study enter patient information into the EDC system to register and allocate the study subjects.

The subject's registration number and the method of laminectomy stabilization (plate method or suture anchor method) will be displayed in the EDC system and also recorded in a printable/downloadable PDF file. Study personnel shall confirm the subject's registration number and the assigned laminectomy stabilization method (plate method or suture anchor method), and record this information in the subject roster or print and retain the PDF containing the assignment results.

2) Allocation Method

- Allocation Method: Minimization Method
- Allocation Adjustment Factors: ① Facility, ② Age, ③ Gender, ④ Preoperative Diagnosis

[Rationale]

① Facility (Institute of Science Tokyo Hospital / Saiseikai Kawaguchi General Hospital / Saku Medical Center)

To account for potential differences between facilities in patient background, short-term outcomes, etc.

② Age (64 years or younger / 65–74 years / 75 years or older)

③ Gender (Male / Female)

Age and gender are common prognostic factors in treatment outcomes for DCM patients.

④ Preoperative Diagnosis (Cervical Spondylotic Myelopathy (CSM) / Ossification of the Posterior Longitudinal Ligament (OPLL))

Treatment prognosis has been reported to differ depending on the pathology.

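### Facility is one of four minimisation factors but the only one left out of the primary ANCOVA and the MMRM, so the non-inferiority interval may be slightly wider than necessary

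*Protocol*

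**What the plan says.** Section 5.3 of the protocol allocates by minimisation and lists the factors: "Allocation Adjustment Factors: ① Facility, ② Age, ③ Gender, ④ Preoperative Diagnosis". Facility has three levels, one per participating hospital, and the stated reason for using it is "To account for potential differences between facilities in patient background, short-term outcomes, etc".

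Section 10.5.2 defines the primary analysis as an ANCOVA of the 1-year recovery rate in the FAS: "The analysis model included the following covariates: group, preoperative JOA score, age", then sex and preoperative diagnosis. Non-inferiority is concluded if the lower 95% confidence limit for the "least squares mean difference between groups at 1 year postoperatively exceeds –20" percent. The supporting MMRM is given in the same way: "The analysis model will include the following as fixed effects: group, time point, group-time interaction, preoperative JOA score, age", then sex and diagnosis. Facility appears in neither list, and the protocol does not say why.

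In section 10.2 the control recovery rate "was set at 50% (standard deviation 40%), with a non-inferiority margin of 20" percent, with one-sided 0.025 significance and 0.9 power. This leads to 172 evaluable patients and 216 enrolled.

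**The concern.** Minimisation makes the arms similar on the chosen factors. If such a factor also predicts the outcome, the true sampling variance of the treatment difference is smaller than an analysis that ignores the factor will report. The model that omits it keeps the between-level variance in its residual, so the interval is too wide and the test is conservative.

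The plan follows the usual principle of analysing by the allocation factors for three of the four and drops the fourth. The cost would be some precision in the comparison that decides the trial. The same gap carries over to the section 10.5.3 analyses that copy the primary model: EQ-5D, VAS, NDI, lamina retention, alignment, paraspinal muscle area and dural sac area.

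This is not simply a detail left to the SAP, because the protocol itself writes out both covariate lists. Section 10 also asks for a protocol revision if a later change to the primary analysis method would materially affect interpretation. In an unblinded trial the covariate set is best settled early.

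**Working it through.** **1. Factors side by side**

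| Minimisation factor (5.3) | Primary ANCOVA (10.5.2) | MMRM (10.5.2) |
|---|---|---|
| Facility (3 levels) | no | no |
| Age (3 classes) | yes | yes |
| Gender | yes | yes |
| Preoperative diagnosis | yes | yes |

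Both models also contain preoperative JOA score.

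**2. The plan's own sample size**

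Inputs from section 10.2: SD 40, margin 20, one-sided 0.025, power 0.90. The true difference is not stated; zero is assumed.

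- Normal approximation: n per arm = 2 × (1.960 + 1.282)² × 40² / 20² = 84.1, rounded up to 85, or 170 in total.
- Noncentral t: 86 per arm (power 0.903), or 172 in total. This is the protocol's figure.
- Dropout: 86 / 0.8 = 107.5, rounded up to 108 per arm, or 216 in total. This also agrees.

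**3. Half-width with and without facility**

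At 172 evaluable patients, equally split, the standard error without facility is SE0 = 40 × √(4/172) = 6.10. The ANCOVA has 7 parameters, so 165 degrees of freedom and t = 1.974. The half-width is 1.974 × 6.10 = 12.04.

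Let R² be the share of outcome variance due to facility. The protocol gives no value, so it is an assumption shown as a range. With facility in the model and balanced between arms, SE1 = SE0 × √(1 − R²), on 163 degrees of freedom (t = 1.975).

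Other quantities, with t taken from the model in question:

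- One-sided type I error without facility ≈ 1 − Φ(t × SE0 / SE1)
- Power without facility ≈ Φ((20 − t × SE0) / SE1)
- Power with facility ≈ Φ(20 / SE1 − t)

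Example at R² = 5%: SE1 = 6.10 × √0.95 = 5.95. Type I error ≈ 1 − Φ(12.04/5.95) ≈ 0.021. Power without facility ≈ Φ(7.96/5.95) ≈ 0.910.

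| Assumed R² | Half-width without | Half-width with | Too wide by | Type I error without | Power without | Power with |
|---|---|---|---|---|---|---|
| 0% | 12.04 | 12.05 | about 0 | 0.024 | 0.904 | 0.904 |
| 2% | 12.04 | 11.92 | 1.0% | 0.023 | 0.906 | 0.909 |
| 5% | 12.04 | 11.74 | 2.6% | 0.021 | 0.910 | 0.918 |
| 10% | 12.04 | 11.43 | 5.4% | 0.019 | 0.915 | 0.931 |

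The 0.024 in the first row is the nominal 0.025 under this normal approximation.

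**4. Simulation check**

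Four-factor minimisation was simulated with an assumed 0.8 biased coin, assumed facility shares of 40/35/25%, 20% random dropout and 4000 runs per scenario. Preoperative JOA was not simulated.

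- Half-widths without and with facility were 12.05 and 12.07 (R² 0%), 12.05 and 11.95 (2%), 12.05 and 11.76 (5%), 12.05 and 11.45 (10%), in line with the table.
- Type I error has a Monte Carlo standard error of about 0.0025, too coarse to show the small shift at 5% (0.0280 both ways). At 10% it was 0.0192 without and 0.0260 with facility.
- At 0%, power was 0.894 without and 0.895 with facility, about two Monte Carlo standard errors (0.005 each) below the calculated 0.904. As the two values are virtually equal, this is not due to omitting facility.

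**The case against.** The strongest reply is that little is at stake. At a 5% share the half-width changes by 0.3 points against a 20-point margin. The error is on the safe side. The 172 follows from an unadjusted two-sample calculation, so none of the planned power depends on adjusting for facility. The planning SD of 40 already exceeds both pilot SDs in section 10.2 (22.8 and 32.9). The table also applies each share to the full SD of 40; if the existing covariates explain part of that variance, the gain in points is smaller. All of this stands, and it limits the point to a modest gain in precision.

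A reader might also infer more than the protocol supports:

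- **That the plan drops the one factor it regards as affecting outcome.** Section 5.3 also describes age, gender and diagnosis as prognostic, in firmer terms, and all three are in the models. Of facility it says only that differences are possible, and it names patient background first, which the other covariates partly capture. Short-term outcomes need not mean the 1-year recovery rate.
- **That surgeon-scored JOA adds site-scoring noise.** Section 8.2 has the surgeon score JOA, but a constant site offset cancels in the numerator of the recovery rate. It remains only in the denominator, and preoperative JOA is already a covariate.
- **That dropout will leave a biasing facility imbalance.** Imbalance from random dropout is chance variation that the interval already covers. Bias would need loss that differs by arm and facility together, and nothing in the protocol points to that.

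These arguments are secondary and unquantified, and the point does not rest on them.

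**Conclusion.** The inconsistency is certain: facility is balanced at allocation and then omitted, alone and without a reason, from both models that section 10.5.2 fixes. Its consequence is conditional. If facility predicts the recovery rate, the interval is about 1% to 5% too wide for an assumed variance share of 2% to 10%. If it does not, the two models are practically equivalent.

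It would be wrong to read this as a threat to the primary conclusion. The omission makes a false non-inferiority claim slightly less likely, not more, and calculated power stays at or above 0.90. The figures rest on the protocol's SD of 40, an assumed zero true difference, 172 evaluable patients split equally, and facility balanced between arms. The variance share is an assumption throughout.

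**What to change.** Add facility as a 3-level fixed effect to the ANCOVA and the MMRM in section 10.5.2, and to the secondary analyses in section 10.5.3 that follow the primary model. If the omission is deliberate, state the reason in the protocol.

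The cost is a small wording change in each model statement and 2 degrees of freedom (165 to 163). If facility turns out not to matter, the half-width grows by about 0.01 points. Sample size, data collection and patient care are unaffected. With only three hospitals there is no sparse-centre difficulty. The change is best made by protocol revision, with the SAP aligned, before outcome data are examined.
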